### Safety reporting

In the PhRASe feasibility study, safety reporting has two functions:

1. To monitor the safety of patients enrolled into the two arms of the trial;

2. To develop robust and practical safety reporting procedures for use in a fully powered multi-centred trial.

A principle of adverse event reporting is that safety should be monitored in both arms of the trial. Harms that occur after the patient has arrived at hospital could be a direct or indirect result of the treatment received in the prehospital environment. In some cases, we will be able to directly attribute the adverse event to the administration of antibiotics in the prehospital environment, but this will not be possible in all cases. We will monitor for the following serious adverse events (SAEs) in all patients up to 1 week:

• Anaphylaxis

• *C. difficile* infection

• Extravasation at the site administration of antibiotics

• Infection/cellulitis at the site of blood culture collection/administration of antibiotics

• Vascular damage at the site of blood culture collection/administration of antibiotics

SAE monitoring will be conducted by the PRSO so that the research team do not see any identifiable information. The PRSO will alert the Principal Investigator at UHW of all SAEs so that they can be assessed for seriousness and relatedness to the intervention. The Trial Manager will report any Suspected Unexpected Serious Adverse Reactions to the Research Ethics Committee, Sponsor, and the TSC’s Chair and Clinicians within 24 h of receiving notification of them. The rest of the TSC will be informed within 1 week, via the Chair.

We expect to capture harms beyond the 1-week follow-up period for SAEs through the outcomes for the trial, i.e. length of stay and mortality. Deaths and ICU admissions will be reported to the Trial Management Group on a three-monthly basis to ensure there are no safety concerns. For safety reporting purposes, this will be checked through routine records—this information will also be captured using the Secure Anonymised Information Linkage Databank, but due to a time lag in this information being available, we must also use alternative sources for interim reporting.

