**Methods/design:**

This is an individually randomised, two-arm feasibility study for a randomised controlled trial with a 1:1 ratio. Sixty paramedics will receive training to assist them to recognise sepsis using a screening tool, obtain blood cultures, and provide IV antibiotics. If sepsis is suspected, paramedics will randomly allocate patients to intervention or usual care using their next sequential individually issued scratch card. Patients will be followed up at 90 days using linked anonymised data to capture length of hospital admission and mortality. We will also collect self-reported health-related quality of life (using SF-12) at this time. We will interview ten patients by telephone and hold a focus group with paramedics, to find out what they think about the intervention.

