### Intervention development

A clinical intervention development group comprising paramedics, doctors, nurses, and pharmacists from prehospital care, emergency medicine, critical care, and microbiology met to define the exact treatment protocol and training methods for paramedics to follow early in the study period. They used clinical and local knowledge, research literature, and guidelines from the Joint Royal Colleges Ambulance Liaison Committee (JRCALC) and UHW. Based on advice from Public Health Wales, cefotaxime will be the antibiotic administered to patients in this feasibility study. The Screening Tool and Study Flowchart can be seen in Fig. 1; the screening tool is an adaptation of The UK Sepsis Trust’s Prehospital Sepsis Screening and Action Tool [17]. We decided only to include patients with Red Flag Sepsis in this feasibility study so that we did not broaden the use of antibiotics unnecessarily, in line with antimicrobial stewardship.

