#### Quantitative

Data relating to clinical outcomes and hospital diagnosis will be obtained from the Secure Anonymised Information Linkage (SAIL) databank. The SF-12 and Quality of Care monitoring forms will be sent out to participants at 90 days (30 days for participants recruited in the last 2 months of the study) along with the Patient Dissent Forms to be returned directly to the research team at SU for data entry. Routine data will be used for paramedic call out information and will be collated by the PRSO. The PRSO will collect basic demographic details, i.e. age and gender, so that we can see whether participants’ baseline characteristics were similar between trial arms (indicating that randomisation was successful), as well as whether all patients who are allocated to intervention have both blood cultures taken and IV antibiotics given (as the paramedics may be unable to obtain blood cultures or give IV antibiotics in some cases). This information will be collected from patient’s WAST Patient Clinical Record.

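### C. difficile infection is monitored for one week, and the routes named for later harms do not identify a non-fatal case after that, so later cases of this listed event go uncounted

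*Protocol article*

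**What the plan says.** All of the safety provisions are in the protocol article under Safety reporting. The window is fixed there: "We will monitor for the following serious adverse events (SAEs) in all patients up to 1 week". Five events follow: anaphylaxis, C. difficile infection, extravasation, site infection or cellulitis, and vascular damage at the site. C. difficile has no longer window of its own. The Principal Investigator is to assess reported events for seriousness and relatedness.

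The section accepts that harm can arise later and names how it will be found: "We expect to capture harms beyond the 1-week follow-up period for SAEs through the outcomes" of the trial, which it gives as length of stay and mortality. It adds one further check, from routine records: "Deaths and ICU admissions will be reported to the Trial Management Group on a three-monthly basis".

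Two other places bear on this. The Abstract sets the outcome period: "Patients will be followed up at 90 days using linked anonymised data to capture length of hospital admission and mortality". Data collection (Quantitative) states: "Data relating to clinical outcomes and hospital diagnosis will be obtained from the Secure Anonymised Information Linkage (SAIL) databank". The Outcomes section lists hospital diagnosis of sepsis or another condition. Neither readmission nor later C. difficile is named as an outcome or as a safety check.

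**The concern.** The sentence on later harms asserts that the trial outcomes will pick them up. For at least one event on the plan's own list they will not, unless the patient dies.

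Two things are at stake. First, adverse events feed progression criterion 3, which asks for a difference of less than 10% between arms. An event counted incompletely in both arms pulls its part of that difference towards zero. Second, the section gives safety reporting a developmental purpose: to produce procedures that a multi-centre trial can use. A procedure that claims to cover later harms, and does not, would be carried forward untested.

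The event is relevant to this trial on the protocol's own terms. Inclusion was limited to Red Flag Sepsis "so that we did not broaden the use of antibiotics unnecessarily", and criterion 4(b) allows progression with up to 30% of randomised patients (100% − 70%) not diagnosed with sepsis in hospital.

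**Working it through.** The protocol gives no C. difficile rate, onset time or expected event count, so there is no figure to reproduce. The first step is reasoning from the text. The second and third are illustrations on assumed inputs.

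**Step 1. What each named source shows for an infection starting after day 7**

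| Case | One-week SAE list | Length of stay | Mortality | Deaths and ICU review |
|---|---|---|---|---|
| Non-fatal, after discharge, no ICU | not counted | unchanged | unchanged | not seen |
| Non-fatal, still in hospital, no ICU | not counted | perhaps longer, no cause attached | unchanged | not seen |
| Non-fatal, ICU | not counted | perhaps longer, no cause attached | unchanged | ICU admission seen |
| Fatal | not counted | no cause attached | death counted | death seen |

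This reads length of stay as the index admission. If days from a readmission were added, they would still carry no diagnosis. The 90-day patient forms do not help: they are the SF-12 and a quality-of-care monitor, not an enquiry about adverse events. The conclusion of this step does not depend on when such infections usually start.

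**Step 2. Possible size of the under-count (illustration)**

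Inputs:
- n = patients per arm: 100/2 = 50 to 150/2 = 75 (Sample size; 1:1 allocation)
- p = C. difficile risk: not in the document, assumed 1–5%
- f = share of cases arising by day 7: not in the document, assumed 25–75%

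Expected cases missed per arm = n × p × (1 − f).
- Smallest: 50 × 0.01 × 0.25 = 0.125
- Middle: 75 × 0.03 × 0.50 = 1.125
- Largest: 75 × 0.05 × 0.75 = 2.81

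The expected shortfall is about 0.1 to 2.8 cases per arm. At n = 75 and p = 3%, the chance of seeing at least one case in an arm is 1 − 0.97^75 = 0.90 with full ascertainment, and 1 − 0.985^75 = 0.68 if half of the cases fall within the week.

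**Step 3. Against the safety criterion**

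Read as percentage points, a 10% difference is 5 patients at n = 50 and 7.5 at n = 75. If f is the same in both arms, the C. difficile part of the observed difference is f times the true one.
- Upper bound within the assumed ranges, with every missed case in one arm: 0.05 × 0.75 = 3.75 points.
- If the extra exposure is confined to the 30% without sepsis, each with 5% excess risk: the true difference is 0.30 × 5% = 1.5 points. Missing 75% of it loses 1.5 × 0.75 = 1.1 points, which is 0.01125 × 75 = 0.84 of a patient.

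Both are well short of 10 points.

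**The case against.** The strongest case against is about consequence. The Outcomes section times antibiotics given by the paramedic or in hospital, so control patients may be treated too, and in confirmed sepsis the contrast may be mainly one of timing. Late cases would then be missed in both arms and the difference between arms would be small. This stands, and Step 3 agrees with it.

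It can also be said that the sentence voices a general expectation, that the criterion refers to adverse events without tying itself to the one-week list, and that its limits are left to the statistical analysis plan. All true, but the sentence still names its routes, and for this event they do not work.

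A third argument is that linked hospital diagnoses could reveal a later infection. They could, for patients readmitted or still in hospital. Safety reporting does not name them for this use, and a case managed in the community would still be missed.

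A reader might infer more than the documents support:
- *That the safety criterion is materially biased.* The gap would have to hide a large difference. For example, a true 12-point difference would show as 6 points at f = 0.5, but 12 points lies outside the assumed 1–5% risk range.
- *That most cases are missed because one week is a small part of 90 days.* Nothing in the document says that cases are spread evenly over that period.
- *That C. difficile is the principal harm under study.* The protocol lists it as one of five events without ranking them.
- *That laboratory results are already part of the linkage.* The nearest item is contamination of blood cultures, which is not C. difficile testing.

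**Conclusion.** The point holds in a limited form. As written, a C. difficile infection after day 7 is not counted as an adverse event, and the routes named for later harms do not identify a non-fatal one. This follows from the text alone.

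The direction is an under-count. Its size cannot be fixed, because rate and onset time are not given. On assumed risks of 1–5% and 25–75% of cases within the week, it is about 0.1–2.8 expected cases per arm. That is unlikely on its own to decide the safety criterion if the 10% is a difference in percentage points, a reading the text does not state. The main cost is to the second purpose of safety reporting: it leaves that purpose incomplete for this event, without defeating it.

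**What to change.** 1. Keep the one-week window for the immediate and site-related events.
2. Ascertain C. difficile infection in both arms over the 90-day outcome period. Use the routine hospital records that the study already checks for interim safety, together with the SAIL hospital-diagnosis data.
3. Report the 90-day count by arm alongside the safety criterion.
4. Replace the sentence on later harms with one stating that non-fatal harms not recorded in these sources are not captured.

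Costs and limits:
- The Paramedic Research Support Officer has a longer record check.
- SAIL data arrive late, as the protocol itself notes.
- Patients who dissent leave the anonymised follow-up, and criterion 6 tolerates dissent of up to 30%. The 90-day count may therefore rest on fewer patients than the one-week check, so its denominator should be shown.
- Events found only in anonymised data cannot readily be assessed individually for relatedness.
- Cases managed in the community would still be missed.

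Few events should be expected even with the longer window. The gain is sound ascertainment and a tested procedure for the full trial.

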## Discussion

Service users have been involved in developing the initial research idea and preparing an application for funding for PhRASe, as well as in decision-making regarding all documentation for PhRASe, particularly the information sheet for patients. Service users will sit on the Trial Management Group and Trial Steering Committee throughout the trial to ensure that patient’s views are considered equally, as well as take part in analysis and dissemination of our findings.

Interviews and focus groups will be used as a source of information to develop the main trial (if warranted), for example, if suggestions are made as to how to improve the trial protocol.

It should be noted that PhRASe is not a Clinical Trial of Investigational Medicinal Product (CTIMP), as we are not testing the efficacy of antibiotics. Rather, we are testing the prehospital collection of blood cultures and administration of antibiotics in a technique which has not been previously tested by paramedics or in the prehospital setting.

We are aware that the nurses’ station in UHW resus, where the randomisation log will be kept during patient recruitment, is a very busy environment. We have taken steps to ensure that the log is not lost—including attaching it to the desk with string and placing a Bluetooth tracker on.

## Abbreviations

CVUHB: Cardiff and Vale University Health Board
ED: Emergency department
EMS: Emergency medical services
IV: Intravenous
JRCALC: Joint Royal Colleges Ambulance Liaison Committee
NHS: National Health Service
PGD: Patient group direction
PRSO: Paramedic Research Support Officer
RCT: Randomised controlled trial
SAE: Serious adverse event
SU: Swansea University
UHW: University Hospital Wales
WAST: Welsh Ambulance Services NHS Trust
